### Health economic evaluation

A prospective health economic evaluation will be embedded within the trial design. The health economic evaluation will adopt a UK NHS and Personal Social Services perspective in accordance with the National Institute for Health and Care Excellence (NICE) Reference Case [33].

Primary research methods designed will mirror those applied in our economic evaluation conducted as part of the TOBY trial [34], and will include capital and non-capital costs of the whole-body hypothermia system, transport costs to tertiary cooling centres, and length of hospital stay. Downstream resource consequences until hospital discharge, including duration and intensity of care provided, will be captured through trial case report forms. In addition, online economic questionnaires completed by parents at 6, 12, 18, and 24 months will document post-hospitalisation resource utilisation. Unit costs for post-hospital discharge resource inputs will largely be derived from national reference tariffs, although primary research that uses established accounting methods may also be required.

The cost-effectiveness of whole-body hypothermia will be expressed in terms of incremental cost per unit change in the cognitive composite score of the Bayley-III examination (cost-effectiveness analysis). Bivariate regression of costs and consequences, with multiple imputations of missing data, will be conducted to generate within-trial estimates of incremental cost-effectiveness associated with whole body cooling. Sensitivity analyses will be undertaken to assess the impact of areas of uncertainty surrounding components of the economic evaluation. The sensitivity analyses will include re-estimation of cost-effectiveness based on cases with complete data, and re-estimation of cost-effectiveness assuming a broader societal perspective. The latter will incorporate direct costs borne by families and friends, for example, travel costs, economic values for informal care provided by family and friends, and economic values associated with productivity losses; the values of these broader resource consequences will be informed by responses to questions in the online parent-completed questionnaires. Cost-effectiveness acceptability curves will be used to show the probability of cost-effectiveness of whole-body hypothermia at alternative cost-effectiveness thresholds with plausible economic values associated with improvements in cognition informed by a literature review.

Decision-analytic modelling, drawing upon our previous decision model developed as part of the TOBY trial [34], will be used to estimate the long-term cost-effectiveness of whole-body cooling with cost-effectiveness expressed in terms of incremental cost per quality-adjusted life year (QALY) gained (cost-utility analysis). Parameter inputs into the decision-analytic model will be informed by our earlier research conducted as part of the TOBY trial, supplemented by targeted literature searches. Approaches for characterising uncertainty, heterogeneity, and distributional effects within the economic evaluation will adhere to the recommendations of the NICE reference case [33]. The economic evaluation will be prospectively planned and detailed within a ‘Health Economic Analysis Plan’ and signed off by the Trial Steering Committee.

### Recordings and reporting of SAEs, SARs and SUSARS

Safety outcomes will consist of measurements of Adverse Events (AEs) and Serious Adverse Events (SAEs) (see section below). If there are sufficient numbers of AEs and SAEs, the Chi-square test or Fisher’s exact test will be used to compare the number of patients with these outcomes between groups. The Mann-Whitney test will be used to compare the number of AEs/SAEs between groups. A list of individual AEs will be reported in each group. All analysis will be performed on a modified Intention to Treat (mITT) basis, using patients with valid outcome data in the analysis. Neonates will be analysed in the groups to which they were randomised (intent-to-treat analysis), regardless of the treatment received.

Monitoring for adverse events of whole-body hypothermia in the intervention group during the intervention period and both groups during the entire length of hospital stay will be conducted by evaluating events described in the secondary outcomes. An additional safety measure will be the appointment of an external Independent Data Monitoring Committee (IDMC) where the progress of the trial and adverse events (AE) will be closely monitored at 4 to 6 monthly intervals, masked to the allocation. The IDMC charter will be finalised and signoff before the start of recruitment.

**The adverse events** will include persistent metabolic acidosis, thrombosis, major bleeding, perforations/ulcerations/bleeding from the rectal probe, hyperglycaemia, hypoglycaemia, necrotising enterocolitis (NEC), thrombocytopenia requiring platelet transfusions, coagulopathy requiring blood products, loss of skin integrity, and hypotension requiring more than 2 inotropes.

**Serious adverse events (SAE)** will include mortality, major cerebral bleeds on MRI, pulmonary bleeds, PPHN requiring inhaled nitric oxide or extra-corporeal membrane oxygenator (ECMO), or any other clinical event the investigators deem as life threatening. Additional SAE reports may be requested (e.g., monthly) throughout the course of the study. Safety will be assessed by the frequency of SAE, and total number of events per baby.

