Separately, a London neonatal transport audit reported that of the 170 babies transported for whole-body hypothermia between 2017 and 2019, 45% had mild HIE or birth acidosis without encephalopathy and did not meet the current criteria for whole-body hypothermia [11].A structured neurological examination to determine severity of HIE prior to initiation of whole-body hypothermia was either not performed or not documented in most babies [11].

Short term outcomes on 7181 babies with mild HIE are available from the Canadian (*n* = 1089; cooled 36%) [12], Californian (*n* = 1364; cooled 71%) [13], Children’s Hospital Neonatal Consortium (*n* = 272; cooled 95%) [14]; US Children’s Hospitals National Database (*n* = 945; cooled 13%) [15] and the UK (*n* = 3511; cooled 30%) [16] registries. These data show that whole-body hypothermia significantly increased duration of ventilatory support (2 days versus 1 day), intensive care stay (9 days versus 6 days), need for invasive ventilation (60% versus 45%), use of opioid infusion (67% versus 12%), disseminated intravascular coagulation (8% versus 2%), hepatic dysfunction (23% versus 11%), cardiac dysfunction (8% versus 2%), discharge home on oxygen (26% vs. 15%) and tube feeding at hospital discharge (22% versus 13%) compared to usual care. Other adverse short-term outcomes noted only in babies with mild HIE who underwent whole-body hypothermia include hypotension (16%), thrombocytopenia (10%), coagulopathy (17%), persistent metabolic acidosis (8%), and subcutaneous fat necrosis (1%). No neurodevelopmental outcome data are available from any of these registries, so the long-term impact is unknown.

A well-designed observational study (COOL Prime Study: Comparative Effectiveness for Cooling Prospectively Infants with Mild Encephalopathy) evaluating the neurological outcomes of 430 neonates with mild HIE from 15 hospitals is currently ongoing in the USA (NCT04621279). However, in the absence of a randomised controlled arm, no conclusions about safety and efficacy of whole-body hypothermia can be made from observational data [17].

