Lack of hypothermic neuroprotection and potential harms reported in two recent major hypothermia trials [18, 19] have highlighted the hazards of therapeutic drift, and the critical importance of conducting clinical trials before extending its use to untested populations. The first of these trials involved 408 neonates with moderate or severe HIE from low and middle-income countries (HELIX; Hypothermia for Encephalopathy in low and middle-income countries) [19], which reported a significant increase in mortality with whole-body hypothermia. The second trial (Preemie Hypothermia trial) included 151 premature neonates with moderate or severe HIE born between 33 + 0 to 35 + 5 weeks and reported that whole-body hypothermia increased the probably of death by 77% [18]. Unlike the original hypothermia trials where hyperthermia occurred in 14–29% of the control arms [20–22], both HELIX trial [19] and PREMIE hypothermia trials had much lower occurrence of hyperthermia in the control arm.

The British Association of Perinatal Medicine (BAPM) [23] and the American Academy of Pediatrics [16, 24, 25] have called for an urgent clinical trial to assess safety and efficacy of hypothermia for mild HIE.

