## Study design

### Setting

Cooling in mild encephalopathy (COMET) is a phase III multi-centre open label two-arm randomised controlled trial (RCT) with internal pilot and masked outcome assessments. Administration of cooling therapy cannot be masked. The trial will recruit from five neonatal operational delivery networks (ODN) involving around 50 to 60 NHS hospitals. The recruitment will occur at both tertiary and non-tertiary (non-cooling) centres, although the neonates recruited from non-tertiary centres will be transferred to a tertiary centre after randomisation.

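### As written, the IDMC reviews adverse events masked to allocation, with no stated route to unmask, so it cannot attribute an excess of harm to cooling during recruitment

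*Protocol article*

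**What the plan says.** The section on recording and reporting of SAEs sets out the committee's role: "An additional safety measure will be the appointment of an external Independent Data Monitoring Committee (IDMC"). It then fixes what the committee sees: "adverse events (AE) will be closely monitored at 4 to 6 monthly intervals, masked to the allocation". The next sentence adds that "The IDMC charter will be finalised and signoff before the start of recruitment". The charter itself is not shown.

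The same section plans between-group tests of adverse events (AEs) and serious adverse events (SAEs), but does not assign them to the IDMC. The one other oversight committee named is the steering committee, which appears only because the health economic plan is to be "signed off by the Trial Steering Committee".

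Under Setting, the design is a "phase III multi-centre open label two-arm randomised controlled trial (RCT) with internal pilot and masked outcome assessments", and the article adds that "Administration of cooling therapy cannot be masked". Assessment and follow-up gives the two-year examination to a small central team unaware of allocation.

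The Introduction sets out why harm is a live question. It describes one recent cooling trial "which reported a significant increase in mortality with whole-body hypothermia" and a second, in premature neonates, with a raised probability of death. It also lists registry complications that were more frequent in cooled babies with mild encephalopathy.

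**The concern.** An independent committee reviews accumulating data mainly to see whether one arm is doing worse and to advise on continuing. To do that it needs events split by arm, and it needs to know which arm is which. An excess in the cooled arm points to harm from the intervention; an excess in the control arm may point to benefit. The stated masking withholds that information.

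Masking would be easier to defend if it protected something, but the gain is small. Clinicians and parents know the allocation, and bias in the primary outcome is handled by masked examiners. A committee that neither delivers care nor assesses outcomes can see allocation without disturbing either.

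The timing adds weight. Recruitment lasts 30 months and the primary outcome is read at 24 (± 2) months, so for most of recruitment short-term safety is the main comparative evidence available. Reviews every 4 to 6 months give 30/6 = 5 to 30/4 = 7.5, that is about 5 to 7 reviews in that period. Under the stated rule, none of them could attribute an excess to cooling.

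**Working it through.** **Inputs**
- Total sample 426 (Sample size calculation), so 213 per arm. Half enrolment is taken as 107 per arm.
- Registry rates, cooled versus usual care (Introduction): disseminated intravascular coagulation (DIC) and cardiac dysfunction each 8% versus 2%; hepatic dysfunction 23% versus 11%.
- Mortality expected below 1% (Primary outcome).
- Assumption: the registry rates carry over to the trial. They are observational and serve only as an illustration.

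**The plan's own figure.** For a 5-point difference, SD 15, 5% significance (two-sided assumed) and 90% power, the t-test solution is 190.1, which rounds up to 191 per group. Allowing for 10% drop-out, 191/0.9 = 212.2, rounded up to 213 per group, or 426 in total. The sample size reproduces, and the point does not rest on an error in it.

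**Reading 1: pooled data.** Expected total = n per arm × (rate cooled + rate control).
- DIC or cardiac dysfunction, full enrolment: 213 × (0.08 + 0.02) = 21.3 events in 426, or 5.0%.
- No difference, 5% in each arm: 426 × 0.05 = 21.3 events.
- SD of the total: √(426 × 0.05 × 0.95) = 4.50 with equal rates; √[213 × (0.08 × 0.92 + 0.02 × 0.98)] = 4.46 with 8% versus 2%.

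Mean and spread are practically the same, so the pooled count carries essentially no information on whether the arms differ.

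**What a view by arm would show**

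| Event | Babies per arm | Cooled | Control | Pooled | Power, normal approximation / Fisher |
|---|---|---|---|---|---|
| DIC or cardiac, 8% v 2% | 107 | 8.6 | 2.1 | 10.7 (5%) | 0.52 / 0.41 |
| DIC or cardiac, 8% v 2% | 213 | 17.0 | 4.3 | 21.3 (5%) | 0.81 / 0.78 |
| Hepatic, 23% v 11% | 107 | 24.6 | 11.8 | 36.4 (17%) | 0.65 / 0.59 |
| Hepatic, 23% v 11% | 213 | 49.0 | 23.4 | 72.4 (17%) | 0.91 / 0.90 |

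Power is for a single two-sided test at 0.05.

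**Reading 2: coded groups A and B.** The committee would see about 17 versus 4 for the first event, so the imbalance is visible. The code does not say which group was cooled, so the direction is hidden. The same holds for deaths: at most 426 × 0.01 = 4.3 are expected, and a 4–0 split has opposite meanings depending on which arm holds the four.

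**Result.** The article does not say which reading applies. Pooled data hide the difference; coded data hide its direction. Neither lets the committee attribute an excess to cooling.

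**The case against.** The strongest reply is that report format, coding and unmasking normally belong in the IDMC charter, which the article mentions and which is not shown. This stands as a limit: the conclusion concerns the masking stated in the article, not what the charter may allow. It does not dispose of the point, because the article makes a positive statement about what the committee sees. If the charter says otherwise, the two need to be reconciled.

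Several stronger readings are tempting, and the document does not support them.

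- *Detection of harm is lost altogether.* It is not. The safety section provides for event monitoring throughout the hospital stay and for additional SAE reports on request. Sites know the allocation, and the Withdrawal criteria let the attending physician, with the site principal investigator, stop the intervention for an SAE. These watch individual babies and do not replace a comparison across 50 to 60 hospitals, so detection is impeded rather than removed.
- *A 4–0 and a 2–2 split of deaths look the same under masking.* That is true only of pooled data. Coded tables show the difference and hide only its direction.
- *The IDMC is the only independent safety body.* The text shown gives no safety role to the steering committee, but its remit is not described and some passages were removed, so this cannot be asserted.

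The figures also have limits. DIC is not a listed adverse event; the nearest item is coagulopathy requiring blood products. The Introduction itself says observational data cannot settle safety. Four deaths is roughly a ceiling, since mortality is expected below 1%. The two cited trials with mortality signals enrolled moderate or severe encephalopathy, in other settings or in premature babies. Nor would unmasking settle every case: a 4–0 split at 213 per arm gives a two-sided Fisher p of about 0.12, and power for 8% versus 2% at half enrolment is only 0.41 to 0.52. These limits affect the illustration. They do not affect the logic that attribution needs the arm.

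**Conclusion.** The concern holds in a bounded form. Under the masking stated in the safety section, and with no unmasking route in the text shown, the IDMC cannot attribute an excess of adverse events or deaths to cooling while babies are being recruited. With pooled data, 8% versus 2% is indistinguishable in expectation from 5% versus 5% (about 21 of 426 either way). With coded data, about 17 versus 4 would be seen without knowing which arm had the 17.

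The reasoning holds whatever the event rates; the sizes assume the registry rates apply. A reader might infer that the committee can never unmask, but the unseen charter may provide for it, and the document cannot decide that. No figure in the plan is wrong. What needs changing is one stated rule, which gives little protection against bias in an open-label trial with masked outcome examiners and weakens a named safety measure.

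**What to change.** In the safety section, replace the masking phrase with a statement along these lines: the IDMC receives AEs, SAEs and deaths by randomised arm in closed session, either labelled or coded with the code available to the committee at any time on request; the trial management group, investigators and outcome examiners do not see the aggregate comparisons by arm.

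Bring the IDMC charter into line. If the charter already provides this, correct the protocol text to match it.

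The cost is a change of wording in the protocol and, if needed, the charter. Reviews are already planned every 4 to 6 months, and no extra babies or procedures are needed. The one practical demand is that closed reports be prepared by a statistician separated from the trial team, so that the comparative data do not reach those running the trial.

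### Probe perforation, NEC, thrombosis and most major bleeding count as SAEs only if unmasked investigators deem them life threatening, so the SAE frequency can undercount them

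*Protocol article*

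**What the plan says.** The section Recordings and reporting of SAEs, SARs and SUSARS gives two lists.

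- **Adverse events.** These "will include persistent metabolic acidosis, thrombosis, major bleeding, perforations/ulcerations/bleeding from the rectal probe". The list continues with high and low glucose, then "necrotising enterocolitis (NEC), thrombocytopenia requiring platelet transfusions", and ends with coagulopathy, skin damage and hypotension. Perforation, NEC, thrombosis and major bleeding carry no grade, stage or severity threshold.
- **Serious adverse events.** The named events are death, major cerebral bleeding on MRI, pulmonary bleeding, and PPHN treated with inhaled nitric oxide or ECMO. The list closes with "or any other clinical event the investigators deem as life threatening".

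On analysis, the section states: "Safety will be assessed by the frequency of SAE, and total number of events per baby". It also plans a comparison of the number of patients with events: "If there are sufficient numbers of AEs and SAEs, the Chi-square test or Fisher’s exact test will be used". Event counts are to be compared by the Mann-Whitney test and individual AEs listed for each group. The data monitoring committee is to review AEs every 4 to 6 months without knowing the allocation.

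On masking, the Setting section says: "Administration of cooling therapy cannot be masked". Masking is stated for the outcome assessments and for the committee's review. No masked adjudication of seriousness is described.

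**The concern.** Whether an event is serious should follow from what happened to the baby, by a rule that works the same way in both arms. Here several of the gravest listed events become serious only when someone who knows the allocation calls them life threatening. A bowel injury that needs surgery, or a thrombosis that leaves lasting damage, does not meet any other stated criterion.

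The other safety summary, the number of events per baby, does not make up for this. No weighting is stated, so one high glucose value and one perforation each add one event.

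This matters because the Discussion says the trial will establish the safety of cooling in mild encephalopathy. The Introduction also gives reason to watch bleeding-related harm: in the registry data it cites, disseminated intravascular coagulation was 8% with cooling and 2% without. Rectal temperature is recorded in both arms, so probe injury can occur in either.

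**Working it through.** **1. Which events depend on opinion.** Setting the two lists side by side:

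| Event | In AE list | Named SAE | Other stated route to SAE |
|---|---|---|---|
| Rectal-probe perforation | yes | no | death, or deemed life threatening |
| NEC | yes | no | death, or deemed life threatening |
| Thrombosis | yes | no | death, or deemed life threatening |
| Major bleeding, cerebral (MRI) or pulmonary | yes | yes | not needed |
| Major bleeding, other sites | yes | no | death, or deemed life threatening |

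The dependence on opinion is complete for the first three and partial for major bleeding.

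**2. Size of the safety comparison.** The article states no rate for these events or for SAEs overall; its only relevant design figure is the sample size. With a difference of 5, SD 15, two-sided alpha 0.05 and 90% power, the t-test calculation gives 190.1, rounded up to 191 per group. Allowing for 10% drop-out, 191 / 0.9 = 212.2, rounded up to 213 per arm, or 426 in total. Both stated figures reproduce.

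**3. What the rule does to the SAE count.** Let n be babies per arm, p the true risk of one of these events in an arm, and q the proportion of them that investigators in that arm deem life threatening. The expected number reaching the SAE count is n × p × q.

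- If q is the same in both arms, the difference in the SAE count is q times the true difference, so it shrinks.
- If q differs between arms, a difference can appear or vanish through classification alone. With equal p, the expected difference is n × p × (q in the cooled arm − q in the control arm).

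**4. Illustrations. Every rate here is an assumption, not a figure from the article.**

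- *Equal q.* Assume p of 2% v 0.5%. Then 213 × 0.02 = 4.26 and 213 × 0.005 = 1.07 babies, a difference of 3.2. With q = 0.5 in both arms this becomes 2.13 v 0.53, a difference of 1.6, so about 1.6 babies drop out of the contrast. Over q from 1 to 0 the loss runs from 0 to 3.2.
- *Unequal q.* Assume p of 2% in both arms. The expected SAE difference is 4.26 × (difference in q), which lies between −4.3 and +4.3 babies although there is no true difference.
- *Extreme case.* Assume all serious harm runs at 4% v 8%. Power with pooled null variance is Φ[(0.04 − 1.96 × √(2 × 0.06 × 0.94 / 213)) / √((0.04 × 0.96 + 0.08 × 0.92) / 213)] = Φ[(0.04 − 0.0451) / 0.0229] ≈ Φ(−0.22) = 41%. If the whole excess lay in events left as ordinary AEs, the SAE rates would be equal and the SAE test would reject only at its 5% error rate.

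These show the mechanism. They do not estimate its size in this trial.

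**The case against.** **The events are still measured.** The section plans a between-group comparison of patients with AEs as well as SAEs, an individual AE listing by group, and AE review by the monitoring committee. A reader might infer that perforation or NEC could go unseen. The documents do not support that. Nor does the article rank SAE frequency above its other safety measures. What remains is narrower: the SAE frequency is one of two measures named in the closing safety sentence, and it rests on the rule criticised here.

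**The article is condensed.** Both lists are introduced as inclusive, and the Data collection tools section leaves variable definitions to a manual of procedures that is not shown. A wider definition may exist. But the SAE list supplies its own residual category, confined to what investigators consider life threatening. That is a stated rule, not a detail left out.

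**Slower reporting.** It is tempting to add that an event classed as an AE reaches the monitoring committee later than an SAE. The article states no faster mandatory route for SAEs; it says only that extra SAE reports may be requested. That inference is not supported.

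**Small counts.** On the assumed 2% v 0.5%, 4 v 1 babies gives a Fisher p of 0.37 and 2 v 1 gives 1.0, so no test result would change. This is fair. With rare events the harm table is read as a description, so its counts should not depend on opinion.

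**The remedy could itself bias.** Making prolonged hospital stay a criterion of seriousness would bring in another unmasked judgement. The cited registry data already show longer intensive care with cooling (9 v 6 days). This stands, and it limits the fix. Labelling every ungraded thrombosis as serious would likewise dilute the category.

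**Conclusion.** The point holds in a limited form. Short of death, rectal-probe perforation, NEC, thrombosis and major bleeding outside the brain and lung reach the SAE frequency only if unmasked investigators consider them life threatening. That frequency can therefore undercount these events, and can do so differently by arm.

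The size cannot be computed, because the article gives neither event rates nor any indication of how often investigators would call such events life threatening. The conclusion rests on the two lists as printed and on the absence of any stated masked adjudication. A full protocol with objective seriousness criteria would answer it.

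The primary outcome is unaffected and the events stay visible as AEs. This is an inexpensive correction worth making, not a threat to the trial's main result.

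**What to change.** In the section on recording and reporting of SAEs, reconcile the two lists in one of two ways:

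1. Name probe perforation, NEC and major bleeding at any site as SAEs, together with thrombosis that meets a stated objective criterion; or
2. Add objective seriousness criteria (fatal, life threatening, needing surgery, causing lasting disability), applied identically in both arms.

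In either case, keep investigator opinion only as an addition to the rule. Use prolonged hospital stay as a criterion only with an objective definition or with adjudication masked to allocation. Report each of these events by arm in the safety tables, whatever its label.

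The cost is wording in the protocol and SAE form and a few more SAE reports. Settling it in advance also avoids having to reclassify events later with the allocation known.
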